**Methods:**

This single-center, double-blind, randomized controlled study will recruit 112 patients scheduled to undergo acoustic neuroma surgery. We will compare the effects of liposomal bupivacaine and ropivacaine on postoperative pain when administered via preincisional infiltration before surgery. The primary outcome is the pain score at 24 h postoperatively. Secondary outcomes include the incidence of postoperative nausea and vomiting, amount of postoperative analgesic consumption, changes in vital signs before and after skin incision, and postoperative recovery scale.

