Acoustic neuroma, also known as a vestibular schwannoma, is a common neurosurgical condition requiring open-cranial surgery. It accounts for approximately 5% of intracranial tumors (12). Given the presence of many critical neural structures near the tumor site, such as the facial nerve, monitoring of neural function is typically required during surgery. This ensures that the tumor is removed while preserving facial nerve function, thereby reducing the incidence of postoperative facial paralysis (13–15). However, intraoperative neural function monitoring restricts the use of muscle relaxants and inhalation anesthetics, posing challenges in anesthetic management (16, 17). To avoid adverse situations, such as pain responses and intraoperative awareness, anesthesiologists often administer higher doses of opioid drugs to compensate for the lack of anesthetic depth. However, excessive opioid use can lead to several complications, including respiratory depression, postoperative nausea and vomiting (PONV), hypercapnia, cerebral vasodilation, increased intracranial pressure, and excessive sedation during the recovery and early postoperative periods (18). Given that patients with acoustic neuromas are already at a high risk of PONV, the use of higher opioid doses further increases the incidence of these adverse reactions (19–21). The use of opioid drugs postoperatively can interfere with early neurological examinations. Additionally, severe pain may necessitate their use as rescue rather than routine analgesics. Therefore, to avoid adverse reactions, patients with acoustic neuromas are not advised to receive intravenous postoperative analgesia. The commonly preferred methods are scalp nerve block and local incisional infiltration. However, a scalp nerve block may cause temporary facial nerve paralysis postoperatively, which is not conducive for intraoperative neural monitoring or early neurological assessment of surgical outcomes. This can directly delay the surgeon’s ability to judge the patient’s condition and may negatively affect recovery (22, 23). Therefore, optimal local incisional infiltration is considered the most favorable pain management method for patients undergoing acoustic neuroma surgery (24). Ropivacaine and bupivacaine are commonly used as local anesthetics for local incisional infiltration in clinical practice. Ropivacaine is an amide-type local anesthetic that is known for its good analgesic effects, minimal adverse reactions, and low cardiac toxicity. However, its duration of action is relatively short (2–6 h), which is insufficient to cover the patient’s entire pain period (25). Bupivacaine is a widely used long-acting local anesthetic with a duration of action of 6–8 h. However, it has higher cardiac toxicity, and its duration of action is insufficient to meet the clinical needs for postoperative analgesia (26). In 2011, the U.S. Food and Drug Administration approved a multilayered, foam-based bupivacaine liposome injection (trade name: Exparel) based on Depo Foam™ technology (27). This formulation encapsulates local anesthetics in a drug delivery system to provide long-lasting analgesia for surgical patients, with effects lasting up to 72 h (28). Bupivacaine liposomes can significantly improve postoperative analgesia in orthopedic, gynecological, abdominal, and plastic surgeries and are safe (29–31).

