
### 2.8 Follow-up

The follow-up period will last for 3 days after surgery. Assessments will be conducted at different time points, including pain VAS score, analgesic drug use and frequency, PONV score, postoperative rehabilitation quality score, postoperative hospital stay duration, and cost. Any perioperative adverse reactions related to the surgical procedure, anesthesia, or medication administration will be documented.

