### 3.3 Secondary outcome

(1)   Postoperative pain VAS scores: pain VAS scores at 48 h and 72 h postoperatively.(2)   Changes in vital signs: the MAP and HR at five time points: T1 (before anesthesia), T2 (at incision), T3 (during drilling of the skull), T4 (at skin closure), and T5 (at the end of the operation).(3)   Intraoperative and postoperative analgesic use: intraoperative and resuscitation room opioid use, postoperative opioid use on days 1, 2, and 3, and the number and dosage of celecoxib administered will recorded. Data will be statistically converted to morphine doses.(4)   Incidence of PONV: the preoperative Apfel risk score includes four items: female sex, history of PONV or motion sickness, non-smoking status, and history of opioid use. The incidence of PONV in patients with 0, 1, 2, 3, and 4 risk factors is 10, 21, 39, 61, and 78%, respectively. The Alfel risk score ranges from 0 to 4, with higher scores indicating a higher risk. PONV will be assessed using the VAS scale (0–10), where 0 indicates no nausea; 1–4 indicates mild nausea; 5–6 indicates moderate nausea; and 7–10 indicates severe nausea.(5)   Extubation time and PACU stay: time to extubation and duration of stay in the PACU after surgery.(6)   Length of postoperative hospitalization and costs: duration of postoperative hospital stay and associated costs during hospitalization.(7)   Postoperative rehabilitation quality assessment: the 15-item Quality of Recovery Scale will be used to assess postoperative rehabilitation quality. On the third day after surgery or prior to discharge, patients will be asked to complete a 15-question questionnaire (Table 2). Response options range from 0 to 10 points, with 0 indicating poor condition and 10 indicating excellent condition.(8)   Other postoperative complications: incidence and nature of other postoperative complications.

**TABLE 2 T2:** 15-item quality of recovery scale (QoR-15).

Question	Score (0–10)
1. Do you feel that your breathing is comfortable?	
2. Is your appetite good?	
3. Are you able to rest sufficiently and feel energetic as a result?	
4. How is your sleep quality?	
5. Are you able to take care of your personal hygiene independently?	
6. Are you able to have normal conversations with family and friends?	
7. Do you feel supported and cared for by the medical staff?	
8. Are you able to engage in normal work or household activities?	
9. Do you feel comfortable and able to manage your emotions?	

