10. Do you feel generally happy?	
11. Do you have severe pain that affects your sleep?	
12. Do you have severe pain that is unbearable?	
13. Do you have nausea or vomiting?	
14. Do you feel tense or anxious?	
15. Do you feel sad or depressed?	

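### The nausea-and-vomiting outcome is measured on a nausea-only scale with no score in the PACU, so vomiting without scored nausea is not counted and early events are not clearly included

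*Protocol article*

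**What the plan says.** The abstract lists "the incidence of postoperative nausea and vomiting" first among the secondary outcomes. Section 3.3 has it as item 4 of 8, opening with "Incidence of PONV: the preoperative Apfel risk score includes four items" and giving the expected incidence by number of risk factors (10, 21, 39, 61 and 78% for 0 to 4 factors).

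The same item fixes the measurement: "PONV will be assessed using the VAS scale (0–10), where 0 indicates no nausea", followed by the bands "1–4 indicates mild nausea; 5–6 indicates moderate nausea; and 7–10 indicates severe nausea". No other instrument for PONV is named.

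Table 1 marks the PONV score at 24, 48 and 72 h, with the PACU column empty. Pain VAS, use of other analgesics, complications and adverse events are marked in the PACU and at all three later times.

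Two other places could pick up vomiting. Section 2.8 says "Any perioperative adverse reactions related to the surgical procedure, anesthesia, or medication administration will be documented". QoR-15 item 13 (Table 2) asks "Do you have nausea or vomiting", once, on the third day or before discharge.

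**The concern.** The named outcome has two components and the scale grades only one of them. The Introduction gives PONV some weight: "Given that patients with acoustic neuromas are already at a high risk of PONV" is part of its argument against higher opioid doses, and it also names vomiting among the factors that can lead to raised intracranial pressure. A reader of the results would take the reported incidence to include vomiting.

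Timing adds to this. Sections 2.7 and 2.9 have an opioid dose given near the end of surgery, so the PACU stay is a relevant window, yet the first PONV score is at 24 h. If that score means nausea at the moment of asking, anything that resolved earlier is lost. If it means the worst since surgery, it is not. The text does not say which.

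At stake is whether the reported PONV incidence measures what its name says. If the definition is settled only after data are in, there is also room to choose among definitions.

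**Working it through.** **1. The plan's own figure.** The only sample-size figure is for 24 h pain: means 2.9 and 3.7, SD 1.4, α = 0.05, power 0.80. Normal approximation, two-sided: 2 × (1.96 + 0.8416)² × 1.4² / 0.8² = 48.07, so 49 per arm. The *t*-test solution is 49.05, so 50. Then 50 / 0.9 = 55.6, so 56 per arm and 112 in total, which is 14 blocks of 8. The stated 50 and 112 reproduce. No precision or power is stated for PONV, and nothing in this calculation depends on it.

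**2. Outcome against instrument.**
- Outcome: incidence of nausea and vomiting.
- Instrument: 0 is no nausea; 1–4, 5–6 and 7–10 are grades of nausea.
- Retching and vomiting appear in no anchor. A patient who vomits without reporting nausea scores 0. The article does not say which score makes a case, but this does not matter here: any cut-off of 1 or more classes a score of 0 as a non-case.

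**3. Schedule.** PONV is scored at 24, 48 and 72 h and not in the PACU. With the recall period unstated, there are two readings. A score of current nausea excludes PACU and early ward events. A score covering the whole interval includes nausea in that period, but still not vomiting as such.

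**4. Other sources of vomiting data.**
- Adverse events and complications are recorded from the PACU to 72 h. No text says that these entries count towards PONV incidence, and item 8 of section 3.3 is worded as other complications, apart from PONV.
- QoR-15 item 13 is a single 0–10 response combining nausea and vomiting at one late time. It cannot yield a 0–72 h incidence or separate the two.

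**5. Direction and scale of the effect, as illustration only.** Let a fraction *s* of true cases be captured, equal in both arms, with no false positives. The observed risks are *s*p₁ and *s*p₂, so the risk difference becomes *s*(p₁ − p₂) and the risk ratio is unchanged. For power with n = 50 per arm I use

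Φ{ (d − 1.96 √[2p̄(1−p̄)/n]) / √[(p₁q₁ + p₂q₂)/n] }

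The risks are adjacent values from the Apfel figures in section 3.3. They are not effects assumed by the trial.

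| Capture *s* (assumed) | 61% vs 39%: difference, power | 39% vs 21%: difference, power |
|---|---|---|
| 1.0 | 22.0 points, 59.7% | 18.0 points, 50.2% |
| 0.9 | 19.8 points, 51.2% | 16.2 points, 44.5% |
| 0.8 | 17.6 points, 43.4% | 14.4 points, 39.0% |
| 0.7 | 15.4 points, 36.3% | 12.6 points, 33.8% |

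Check of one cell (*s* = 0.8, 61% vs 39%): risks 0.488 and 0.312, d = 0.176, p̄ = 0.40; 1.96 × √(0.48/50) = 0.1920; √(0.4645/50) = 0.0964; (0.176 − 0.1920)/0.0964 = −0.166; Φ = 0.434.

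Even with full capture, the 95% half-width for 61% vs 39% is 1.96 × √(0.4758/50) = 0.191, or about 19 points.

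**The case against.** The strongest reply is that this is one secondary outcome in a condensed article, that the case definition and recall wording may sit in the full protocol or case report form, and that vomiting has other routes into the data. Part of this stands. The missing cut-off alone would not be a finding. What the article does state, however, is a scale that cannot register vomiting, under a title that includes it, and none of the other routes is tied to the outcome.

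Four stronger readings are tempting and are not supported:
- **That PACU events are missed.** The 24 h score may look back over the whole first day, and adverse events are recorded in the PACU. The supportable statement is that such events are not clearly included.
- **That several other symptom scales are taken in the PACU while PONV is left out.** Among symptom scales only Pain VAS is; QoR-15 is marked only at 72 h.
- **That the Apfel score is collected and then ignored, with PONV fixed to an unadjusted chi-square test.** The score is described in section 3.3 but is not in the baseline list (3.1) or Table 1, so it is not clearly a collected item. Section 4 lists several tests for the remaining outcomes, to be chosen as appropriate. Covariate adjustment may sit in an analysis plan that is not shown, and leaving it out of a randomized comparison is not an error.
- **That a specific, large dilution follows.** No capture rate can be drawn from the document, and equal under-capture without false positives leaves the risk ratio unchanged.

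**Conclusion.** The point holds as a mismatch between a named secondary outcome and the way it is measured. Followed as written, vomiting or retching without scored nausea is not counted, and early PACU events are of uncertain status. The conclusion about vomiting needs no assumption beyond the printed anchors. The conclusion about the PACU rests on the blank cell in Table 1 and the unstated recall period.

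The size is unknown. The table under the working shows only how power for a risk difference would fall under assumed capture rates of 70 to 100%, equal in both arms. The primary outcome, its analysis and the sample size are untouched. It is worth correcting because PONV heads the abstract's secondary outcomes and the remedy is cheap.

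**What to change.** - Define a PONV case as any nausea (score of 1 or more), retching or vomiting from PACU arrival to 72 h.
- Add a PONV entry in the PACU to Table 1 and the case report form, and word each later assessment as covering the time since the last assessment.
- Add one yes/no item for vomiting or retching at each assessment.
- Report vomiting separately from nausea severity, alongside the combined incidence.
- State whether vomiting recorded only as an adverse event counts as a case.
- Optional: if the Apfel score is recorded, as section 3.3 implies, list it as a baseline item and add an Apfel-adjusted analysis of PONV incidence, for example by logistic regression.

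Cost: one extra item, one extra entry and a few lines of text. For patients already enrolled, vomiting and PACU events would need chart review, which may be less complete than prospective questioning. The number of patients classified that way should be reported by arm. The definition should be fixed before unblinding.

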#### 2.4.3 Withdrawal criteria

(1)   Delayed extubation after surgery or admission to the intensive care unit with endotracheal intubation(2)   Need for second operation within the postoperative operation(3)   Poor postoperative cognitive function within 72 h

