### 2.7 Anesthesia management

An identical anesthesia management technique will be used for all patients. Upon admission to the operating room, continuous monitoring of the patient’s vital signs will commence, including ECG, non-invasive blood pressure, HR, and oxygen saturation. Subsequently, peripheral venous access will be established, and invasive blood pressure monitoring will be initiated via femoral artery cannulation under local anesthesia. The nasopharyngeal temperature will also be monitored following intubation. Preoxygenation is a critical component of anesthesia induction. This involves the administration of intravenous propofol at a dosage of 2 mg/kg, sufentanil at 0.25 μg/kg, and rocuronium at 0.6 mg/kg. Following endotracheal intubation, we will utilize a combination of intravenous and inhalational anesthesia. Desflurane will be set at 0.4 MAC, and propofol will be maintained between 2–4 μg/mL to ensure that the bispectral index values remain within the range of 50–60. This parameter will serve as an indicator for monitoring the depth of anesthesia. The ventilation mode is configured for volume control ventilation, with adjustable parameters that include an FiO_2_ level of 60%, a tidal volume (VT) ranging from 6 to 8 mL/kg, and a respiratory rate set between 10 and 15 breaths per minute to maintain end-tidal carbon dioxide levels within the range of 35–45 mmHg. Given the extended duration of acoustic neuroma surgery, intraoperative monitoring of neurological function is imperative. Given that the use of muscle relaxants may interfere with this monitoring process, no additional muscle relaxants will be administered during the procedure. Before the skin incision, 5–10 μg of sufentanil will be administered to the patient based on their weight and current circulatory status. A routine dose of 10 μg of sufentanil will be given to the patient 30 min prior to the conclusion of surgery. Palonosetron (0.25 mg) will be administered prior to skin closure to prevent nausea and vomiting. Continuous infusion of remifentanil (0.15–0.3 μg/kg/min) will be utilized for intraoperative analgesia. This infusion will be gradually tapered off and discontinued 30 min before the end of surgery. The infusion rate of remifentanil will be adjusted to maintain mean arterial pressure (MAP) and HR within ±20% of the baseline values. During recovery, sugammadex will be employed for muscle relaxant antagonism. Intraoperative hypotension will be managed with ephedrine (6 mg) or epinephrine (40 μg). The treatment of bradycardia (<50 bpm) will involve the administration of atropine in a bolus dose of 0.01 mg/kg. If sympathetic excitation occurs, in addition to deepening anesthesia, nimodipine or esmolol may be used to maintain blood pressure and HR within normal ranges. Following the procedure, the patient will be transferred to the post-anesthesia care unit (PACU), where both anesthesiologists and nurse anesthetists will be responsible for the extubation and monitoring of the patient’s condition. The extubation criteria include achieving a VT of 5 mL/kg and a respiratory rate of 12 breaths per min, while ensuring that the patient awakens with a clear swallowing reflex. Additionally, oxygen saturation must remain at or above 95% after breathing room air for 5 min.

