## 4 Statistical methods and sample size

Data analyses will be performed using IBM SPSS Statistics version 20. In addition to the primary analysis, multivariable linear regression will be performed to adjust the primary outcome (24-h VAS score) for potential confounding variables, including age, sex, BMI, ASA physical status, duration of surgery, and tumor size. Exploratory subgroup analyses based on these factors will be conducted if the sample size permits. Normally distributed data will be reported as mean ± standard deviation (mean ± SD), while non-normally distributed data will be presented as median (N) with interquartile range. Categorical data will be shown as percentages (%). Pain scores at different time points will be compared using independent sample *t*-tests, and group comparisons will be analyzed using repeated-measures chi-square analysis. Other metrics will be assessed using χ^2^ tests, *t*-tests, or Mann–Whitney U tests as appropriate. A *p*-value < 0.05 will be considered statistically significant.

Based on prior literature (33), the parameters are set as follows: β = 0.2, α = 0.05, *R* = 1, μ1 = 2.9, μ2 = 3.7, and σ = 1.4. The sample size is calculated using PASS 15.0 statistical software, resulting in 50 effective cases per group. Considering the potential sample loss of 10% and the block size, 112 patients will be enrolled in this study.

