## 6 Data monitoring and management

The study will establish a Data Safety Monitoring Board (DSMB) comprising 10 senior anesthesiologists, surgeons, and statistical experts, each with over 20 years of clinical experience. The DSMB will periodically evaluate the safety of the study, verify the authenticity and integrity of the data, and assess the reliability of implementation procedures. The trial will undergo an annual review by the Ethics Review Committee of Shanghai First People’s Hospital. During this period, the trial will be placed on hold, and participants will not be involved in the review process. Following the review, the trial will either resume or remain suspended based on the audit outcomes. All participants will sign a confidentiality agreement to ensure individual accountability for the accuracy of the data they provide, to maintain data confidentiality, and to protect the privacy of their personal information. All participant information and data will be meticulously recorded in a case report form. Participants who discontinue or deviate from the intervention protocols will not be replaced. Their data will be retained until study completion, except for those who cannot complete the primary outcome assessment. Upon collection and organization, the data will be securely transferred to the principal investigator for storage throughout the duration of the study. Access to the data will be strictly limited to the principal investigator. Other researchers who require access to study data may contact the principal investigator after the completion of the trial to request access, subject to approval and appropriate data-sharing agreements.

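### Undefined delayed extubation is a withdrawal criterion while time to extubation is a secondary outcome: unless withdrawn patients stay in that analysis, it is truncated after randomisation and biased in a direction not known in advance

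*Protocol article*

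**What the plan says.** Section 3.3, item (5), of the protocol article lists as a secondary outcome "time to extubation and duration of stay in the PACU after surgery". Table 1 schedules this assessment in the PACU column only. Section 2.7 places extubation there too, in the unit "where both anesthesiologists and nurse anesthetists will be responsible for the extubation and monitoring of the patient’s condition".

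The first withdrawal criterion in section 2.4.3 is "Delayed extubation after surgery or admission to the intensive care unit with endotracheal intubation". The article does not say how long an extubation must take to count as delayed.

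Section 6 has the only data-handling rule for patients who leave the planned course: "Participants who discontinue or deviate from the intervention protocols will not be replaced". It continues: "Their data will be retained until study completion, except for those who cannot complete the primary outcome assessment". It does not say whether a patient withdrawn under 2.4.3 falls under this rule.

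For secondary measures without a named test, section 4 states: "Other metrics will be assessed using χ^2^ tests, *t*-tests, or Mann–Whitney U tests as appropriate".

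**The concern.** Delayed extubation and intubated intensive care admission can be known only after randomisation and infiltration, and both are extreme values of outcome (5). A rule that withdraws these patients selects on the outcome. If they then leave the analysis, each arm loses its slowest recoveries. An arm with more of them loses more of its worst values and looks better than it was.

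This differs from the effect of the same withdrawals on the 24 h VAS. A patient who is still intubated cannot rate pain, so some loss there is unavoidable. Extubation time can be recorded whether or not the patient can rate pain, so losing it is avoidable.

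With no threshold, 'delayed' is left to judgement, and the effective cut-off need not be the same for every patient.

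**Working it through.** **1. The plan's own figure.** The only sizing is for the 24 h VAS: "β = 0.2, α = 0.05, *R* = 1, μ1 = 2.9, μ2 = 3.7, and σ = 1.4". The normal approximation gives n = 2 × (1.960 + 0.842)² × 1.4² / 0.8² ≈ 48.1, so 49 per group. The t-test solution is 49.05, which rounds up to the stated 50. Then 50 / 0.90 = 55.6, so 56 per group and 112 in total, which is 14 blocks of 8. The figure reproduces but says nothing about extubation time. It does fix the loss allowance: 112 − 100 = 12 patients, or 10.7%.

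**2. What happens to a withdrawn patient's extubation time.**

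- *Extubated late in the PACU, gives a 24 h VAS.* Withdrawn under 2.4.3. Retained if section 6 covers such withdrawals, which it does not say.
- *Still intubated at 24 h.* Withdrawn under 2.4.3. Cannot give the 24 h VAS, so the section 6 exception applies and retention is not assured. These are the longest times.
- *Sent to intensive care intubated, bypassing the PACU.* Withdrawn under 2.4.3. Table 1 has no scheduled place to record the extubation, and there may be no PACU stay to measure.

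**3. Direction of the bias if they leave the analysis.** The documents give no mean, SD, cut-off or rate, so every input here is assumed. For lognormal times with median m and log-SD s, the full mean is m·exp(s²/2). The mean below a cut-off c is m·exp(s²/2)·Φ(z − s)/Φ(z), with z = ln(c/m)/s. One cut-off applies to both arms, set so that 2%, 5% or 10% of all patients are removed. Differences are arm 2 minus arm 1, in minutes.

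| Assumed arm 1 vs arm 2 | Full | 2% removed | 5% removed | 10% removed |
|---|---|---|---|---|
| Normal, means 20 vs 25, SD 10 | 5.00 | 4.52 | 4.10 | 3.61 |
| Lognormal, medians 20 vs 25, log-SD 0.5 | 5.67 | 4.64 | 3.93 | 3.20 |
| Lognormal, identical arms | 0 | 0 | 0 | 0 |
| Lognormal, median 18, log-SD 0.6 vs median 20, log-SD 0.4 | 0.12 | 1.54 | 2.16 | 2.53 |
| Lognormal, median 18, log-SD 0.8 vs median 20, log-SD 0.4 | −3.12 | +0.19 | +2.19 | +3.48 |

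*Second row at 10%:* c = 43.1 min removes 6.2% of arm 1 and 13.8% of arm 2. The means fall from 22.66 and 28.33 to 20.54 and 23.74. The difference falls from 5.67 to 3.20, and 1 − 3.20/5.67 = 44%.

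*Last row at 10%:* c = 40.1 min removes 15.9% of arm 1 and 4.1% of arm 2. Arm 1, slower on average because of its tail, then appears faster.

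Under a simple shift the loss is 10% to 28% (normal) or 18% to 44% (lognormal). With unequal tails the difference grows or reverses.

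**The case against.** **Exclusion is not stated.** A reader might infer that the slowest patients cannot be scored at all. The article does not say so. Section 2.4.3 names reasons for withdrawal, not deletion of data, and section 6 leans towards retention for anyone who gives a 24 h VAS. Under an assumed median of 30 min and log-SD of 0.9, the chance of exceeding 1,440 min is about 0.00001 (z = ln 48 / 0.9 = 4.3). Cut-offs that remove 3% to 10% of a control arm with that median (log-SD 0.5 to 0.9) lie at about 57 to 163 min. Such patients could rate pain at 24 h and would be kept if section 6 applies. This stands against the strong reading. It does not settle the matter, because section 6 is not tied to 2.4.3.

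**The difference need not shrink.** A reader might also infer that truncation always pulls the comparison towards zero. That needs a simple shift and a common cut-off. Section 2.4.3 fixes no cut-off, and the last two table rows show the opposite.

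**The stakes are limited.** This is one of eight secondary items, and the trial is sized only for the 24 h VAS. In simulations with 56 per arm, a true ratio of 0.80 and log-SD 0.5 to 0.9, Mann-Whitney power was only 25% to 63% even with every patient kept. Dropping the slowest 10% of controls, with the same cut-off in both arms, cost 6.5 to 14 points. That case spends nearly the whole loss allowance on delayed extubation, leaving almost none for reoperation, poor cognition or ordinary loss. Nothing in the article shows that either drug alters awakening. All this stands.

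**An article may leave scoring rules to the full protocol or SAP.** True of scoring detail alone. Here two stated provisions conflict: one defines the outcome and the other withdraws patients on its value.

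**Conclusion.** The point holds as a conflict between sections 2.4.3, 3.3 item (5) and 6. Withdrawal depends on the outcome's own value, and no rule clearly keeps withdrawn patients in its analysis. If they leave it, outcome (5) is truncated after randomisation and the arm comparison is biased: towards no difference under a shift with a common cut-off, in either direction otherwise. If they are kept, the bias does not arise.

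The size cannot be established from the article. The percentages rest wholly on assumed distributions and removal rates, and show only that a few per cent removed can matter. The primary outcome's sample size is untouched by this point. It should be corrected because the remedy is cheap, but it does not threaten the trial's main conclusion.

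**What to change.** - Reconcile 2.4.3, 3.3 item (5) and section 6 by stating that withdrawal for delayed extubation or intubated intensive care admission does not remove a patient from outcome (5). Say what counts as delayed.
- Record the actual extubation time for every randomised, infiltrated patient wherever extubation happens, and amend Table 1 to match.
- Compare arms with the Mann-Whitney test already named in section 4, and report medians.
- Report the numbers of delayed extubations and intubated intensive care admissions by arm.
- Limit the section 6 exception so that a missing 24 h VAS does not drop extubation data.
- For patients who bypass the PACU, choose in advance how PACU stay is handled. Assigning the worst rank is one option; reporting them separately by arm is another.

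The cost is a few sentences of protocol or SAP wording. Extubation time should already be in the clinical record, so no extra patients or visits are needed. The downside is more skewed times, summarised by median and rank test rather than mean and t-test.
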